### Feasibility

In Sri Lanka, thyroid cancer has become the third most common cancer next to breast and oral cancer [16–18]. Furthermore, the incidence is increasing at a considerable rate. Each year, around 1600 patients are diagnosed of thyroid cancer of which around 500 are referred to the National Cancer Institute for RAI [18].

### Protocol waiver/deviations/violation

Any deviations from the protocol will be described and justified as a protocol amendment or in the final report. Changes and amendments to the protocol will only be made by the study committee. Approval of amendments by the institutional ethical review committee will be required prior to their implementation. The investigators will obtain approval/advice for the revised consent form from the ethics committee prior to implementation of the change/s. In addition, changes to the questionnaires and re-consenting, if required, will be incorporated in the amendment. Any changes to the protocol will be communicated to interested parties such as investigators and the trial registry through the official email address and also directly during research team meetings either in person or online. The investigator will not implement any changes to or deviations from the protocol except where it is essential to eliminate immediate hazard(s) to study subject(s).

The privacy and confidentiality of medical information will be maximized. There will be no biological specimens collected for this study. The study will be conducted in accordance with applicable privacy acts and regulations. No participant identifiers will be used in data collection. However, age, ethnicity, sex, diagnosis and stage will be collected. All data generated in this study will remain confidential and only anonymized data will be used in publications. Participants will be informed that completed questionnaires will only be seen by authorized members of the research team. Study data will be collected on the questionnaire forms and will then be transferred into a password-protected computerized database maintained at the Department of Surgery, Faculty of Medicine, Colombo. Data will be kept for a period of 1–3 years after completion of the study and thereafter deleted. Only data collectors and study investigators will have access to the database. Trial results will be communicated to the participants and via scientific publications in peer-reviewed journals and presentations at scientific fora.

### Safety of caregivers and health care providers

Patients treated with high doses of radioactive iodine are isolated for 3–5 days to prevent exposure to caregivers (including health care staff). To prevent exposure of caregivers and health care providers to radiation, the tablets for the 3-day period will be given to the patient before administration of radioactive iodine and will be instructed to take the medications at the scheduled time. Patients will be monitored whether they are taking the medications through phone calls. This will minimize the exposure of care givers and health care staff.

All adverse events, which occur whilst the participant is enrolled on the trial, will be reported in the patients’ medical records and recorded on the relevant case form. The Common Terminology Criteria for Adverse Events (CTMAE version 4.0—see appendices) will be used to grade the severity of an event.

### Data and Safety Monitoring Board (DSMB)

The primary responsibilities of the DSMB will include periodical review and evaluation of the study data for participant safety, study conduct and progress and make recommendations to investigators and relevant other parties concerning the continuation, modification or termination of the trial. The DSMB will consider study-specific data as well as relevant background data about the differentiated thyroid CA, RAI treatment, use of prednisolone and patient population under study.

During the trial, the DSMB will review cumulative study data to evaluate safety of prednisolone, study conduct and scientific validity and integrity of the trial. DSMB members will look into the timeliness, completeness and accuracy of the data to ensure safety and welfare of study participants. The DSMB will also assess the performance of overall study operations and any other relevant issues, as necessary. Members of the DSMB will meet every 8 weeks to review the study data and make recommendation to the research team on conduct of the study. The DSMB will include three independent experts in the field (Supplementary file).

### Data analysis

#### Sample size calculation

The reported rates of radiation thyroiditis are approximately 20% whilst acute radiation sialadenitis is 12–67% and chronic sialadenitis and xerostomia were 20% [5, 6]. Based on these available data, we assume that clinically significant adverse effects will be reported at 3 months in 20% of patients. At a 2-sided 5% alpha level, a total of 200 patients in each group is required to ensure an 80% power if glucocorticoids are associated with a 10% absolute reduction (10% vs. 20%).

### Statistical analysis

Analyses will be performed in accordance with the intention-to-treat analysis principle.

All randomized participants randomized to study and control groups will be included in the main analyses irrespective of protocol adherence (i.e. intention-to-treat analysis). An additional per-protocol analysis will also be conducted only including the patients who adhered to the treatment protocol with completed follow-up. For each patient, the maximum grade for all types of events will be calculated over the whole observation period. The maximum grades per patient will be tabulated, first considering all adverse effects, then focusing on clinically relevant adverse effects as defined in Table 1 (primary endpoint). The proportion of patients who have experienced clinically relevant adverse effects will be estimated in each group. Difference of proportions between the 2 treatment groups as well as odds ratio will be provided to estimate the impact of glucocorticoids on the risk of clinically significant RAI therapy-related adverse effects. All these estimates will be provided with their 95% confidence intervals. Analyses will be adjusted on the stratification factors. Comparisons between groups on binary endpoints will be performed using a logistic regression, and comparisons between groups on continuous endpoints will be performed using *t* tests. The *p* value will be evaluated at the 5% level of significance. No adjustment will be made for multiple comparisons associated with secondary analyses, but these will be evaluated in proper context and fully reported.

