#### Randomization (or stratification) procedures

At study entry, patients will be randomly allocated to one of the two arms, the intervention arm and the placebo arm. Randomization will be balanced (1:1), using permuted blocks, and stratified according to the total dose of RAI given for stratification into three groups. Criteria for stratification will be 50–100, > 100 and < 200, and > 200 mCi.An independent investigator will be responsible for randomization of treatment using an online randomization software, ensuring concealment of treatment allocation for the next patient.

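### Optional gain, not an error: the primary model could also adjust for baseline symptoms, which are recorded anyway, for about 0 to 3 points of power

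*Protocol article*

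**What the plan says.** The Statistical analysis section of the protocol article fixes both the method and the adjustment set: "Comparisons between groups on binary endpoints will be performed using a logistic regression", and "Analyses will be adjusted on the stratification factors". It reports two effect measures: "Difference of proportions between the 2 treatment groups as well as odds ratio will be provided".

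The randomization section makes dose the only stratification factor: "Randomization will be balanced (1:1), using permuted blocks, and stratified according to the total dose of RAI given". The bands are also given: "Criteria for stratification will be 50–100, > 100 and < 200, and > 200 mCi". No other covariate is named for the primary analysis, and none is ruled out.

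The Baseline evaluation section schedules a symptom analysis, an oral and eye examination, EQ-5D-5L and FACT H&N before treatment.

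The sample size is an unadjusted comparison of two proportions. On the control rate it says "we assume that clinically significant adverse effects will be reported at 3 months in 20% of patients", and on the result "At a 2-sided 5% alpha level, a total of 200 patients in each group is required to ensure an 80% power", for a fall to 10%.

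**The concern.** The primary endpoint is a composite of neck, oral, gastrointestinal and eye symptoms. Three features make a patient's baseline state plausibly prognostic:

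- **Population.** Every patient has had a total thyroidectomy.
- **Eligibility.** Previous salivary gland and eye disease, gastric and duodenal ulcers, and previous major head and neck surgery are excluded. No criterion names existing neck pain or swelling, dysphagia, taste change, nausea or dyspepsia, and all of these are Table 1 components.
- **Endpoint definition.** Under Primary outcome, a Table 1 symptom of any severity counts if it lasts more than 2 weeks, and dyspnoea counts at any grade. A mild complaint that was already present could therefore bear on the outcome.

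A prognostic baseline variable that is collected but left out of the model is a small missed opportunity. The margin over the calculated sample size is one patient per arm, so even a modest gain has some use. What is at stake is efficiency and protection against chance imbalance; validity is not in question.

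**Working it through.** **Inputs from the protocol:** 20% versus 10%, two-sided 5%, 200 per arm, 1:1, three dose bands.

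**Inputs assumed, because the protocol gives none:** prevalence *q* of a baseline symptom, 5 to 30%; odds ratio between that symptom and the endpoint, 2 to 5. The marginal risks are held at 20% and 10% throughout.

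**1. The plan's own figure.** With pooled variance and mean risk 0.15:

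n = [1.960·√(2·0.15·0.85) + 0.8416·√(0.20·0.80 + 0.10·0.90)]² / 0.10² = (0.9897 + 0.4208)² / 0.01 ≈ 199 per arm.

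Power at 200 per arm is 80.2%. The stated figure is reproduced with no covariate gain assumed.

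**2. Standardised risk difference.** Without the covariate, the variance is (0.16 + 0.09)/200 = 0.001250. With a binary covariate it is the mean within-level binomial variance in each arm divided by 200, plus the variance of the level-specific differences divided by 400.

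Worked case, *q* = 30% and odds ratio 3. Solving for the marginal risks gives these risks without and with the symptom: control 0.1429 and 0.3333, prednisolone 0.0669 and 0.1771.

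- Control: 0.7·0.1429·0.8571 + 0.3·0.3333·0.6667 = 0.1524
- Prednisolone: 0.7·0.0669·0.9331 + 0.3·0.1771·0.8229 = 0.0875
- Differences −0.0759 and −0.1562 around −0.10: 0.7·0.0241² + 0.3·0.0562² = 0.00135
- Variance: (0.1524 + 0.0875)/200 + 0.00135/400 = 0.001203
- Ratio: 0.001203/0.001250 = 0.962, equivalent to 400·(1 − 0.962) ≈ 15 patients

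**3. Logistic test.** Without the covariate, the log odds ratio is ln(0.111/0.25) = −0.811. Its SE is √(1/(200·0.16) + 1/(200·0.09)) = 0.295, and Wald power is 78.6%. This is lower than 80.2% because the Wald test on the log odds scale is not the pooled test of step 1. The expected-information calculation was repeated with the covariate. Separately, 6000 trials per scenario were simulated with the dose bands in both models; the bands had no effect on the simulated outcome.

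| Prevalence, odds ratio | Risk-difference variance ratio | Equivalent patients of 400 | Wald power without → with | Simulated power without → with |
|---|---|---|---|---|
| 5%, 2 | 0.996 | 2 | 78.6 → 78.8% | 80.4 → 80.3% |
| 10%, 3 | 0.978 | 9 | 78.6 → 79.4% | 80.4 → 81.3% |
| 30%, 3 | 0.962 | 15 | 78.6 → 80.1% | 80.1 → 81.1% |
| 30%, 5 | 0.918 | 33 | 78.6 → 81.8% | 80.8 → 83.9% |

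The Monte Carlo error of each simulated power is about √(0.8·0.2/6000) = 0.5 points, so the first row shows no gain.

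**4. Where the gain comes from.** The SE of the log odds ratio does not fall. By expected information it goes from 0.295 to between 0.295 and 0.308. Power rises because the conditional log odds ratio moves away from zero, for example from −0.811 to −0.843 at 30% and odds ratio 3. Precision in the ordinary sense improves only for the standardised risk difference.

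**The case against.** The strongest reply is that nothing here is wrong. Adjusting for the stratification factor is valid, matches the randomization, and delivers the power the sample size promises. Further prognostic covariates are often left to a statistical analysis plan, which is not shown and may already name them. All of that stands, and it is why the point is optional.

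Three further objections also stand and limit its size:

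- **Eligibility and screening.** The exclusions, with an oral and eye examination at screening for disease resembling the Table 1 effects, remove much of the baseline variation. A prevalence of 30% has no support in the protocol.
- **Endpoint.** The primary outcome requires onset and attribution to RAI, so an existing complaint is not automatically an event. This weakens the link but leaves it to clinical judgement.
- **Covariate definition.** Table 1 also contains rows related to glucocorticoids alone (infections, hyperglycaemia, altered sensorium, sleep, mood). These are not components of the RAI endpoint and do not belong in the term. The article does not say that baseline symptoms are CTCAE-graded, so a yes/no term is safer than a graded one.

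A reader might infer that the plan gives up material precision, or that the trial is underpowered without the extra term. The protocol supports neither: the power calculation does not rely on any covariate, and no prognostic strength is given from which a material loss could be shown.

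**Conclusion.** This is a free improvement and not an error. The primary analysis as stated is valid and has its planned power. Adding one pre-specified baseline symptom term would gain about 0 to 1 point of power in moderate scenarios, and about 3 points with 30% prevalence and an odds ratio of 5, which is an extreme case. The variance of the standardised risk difference would fall by about 0 to 8%. These sizes rest wholly on the assumed prevalence and odds ratio.

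It would be tempting to say that adjustment sharpens the odds ratio itself. It does not: the adjusted odds ratio is a different, conditional quantity with an equal or slightly larger standard error. If the analysis plan already names a baseline symptom covariate, the point is met.

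**What to change.** In the Statistical analysis section, before recruitment starts:

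- Pre-specify the primary logistic model as treatment + RAI dose stratum + presence at baseline of any RAI-related Table 1 symptom (yes/no). Keep the rows shared between RAI and glucocorticoids, and leave out the glucocorticoid-only rows.
- Obtain the difference of proportions and its 95% confidence interval by standardisation from that model.
- Label the odds ratio as conditional on the dose stratum and baseline symptom status.
- Keep the stratum-only model as a sensitivity analysis.

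The cost is a few sentences, plus a check that the baseline form records presence or absence of each RAI-related Table 1 symptom. No extra visit, instrument or patient is needed. Trial status says recruitment had not begun, so the choice can be fixed before any outcome is seen.

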## Discussion

The adverse effects of RAI may be long lasting and may considerably impact the quality of life of patients. The treatment of adverse effects of RAI is mainly symptomatic. This includes proper hydration, use of sialagogues, antiemetics and proton pump inhibitors, and in cases of inflammatory tumour expansion, glucocorticoids may be administered [5, 6]. This is the first randomized control clinical trial designed to assess the effectiveness of prophylactic steroids in reducing the adverse effects of RAI. We hypothesize that a short course of prophylactic prednisolone would be beneficial in reducing the early and intermediate adverse effects of RAI.

Glucocorticoids have significant anti-inflammatory and immunosuppressive properties through its genomic and non-genomic effects [19]. Due to its effect of reducing serum IgG after RAI therapy, this might reflect a decrease of any potential immune-mediated cytotoxicity elicited by the radiation [20]. Furthermore, glucocorticoids may also have a direct radioprotective effect by reducing the intracellular oxidative stress, but it needs further clarification [20]. Also, inflammatory tumour expansion is implicated in the pathogenesis of certain adverse effects such as neck swelling and tracheal compression [6]. Therefore, a short course of glucocorticoids is recommended in patients with symptoms of neck swelling and discomfort following RAI which is seen in large thyroid remnants [6, 21]. Furthermore, glucocorticoid prophylaxis has been recommended in cases where thyroid tumour deposits are suspected near vital structures or in confined anatomical spaces such as the brain, spinal cord, lungs or bone to prevent or minimize the effect of inflammatory tumour expansion [6, 21]. Probable adverse effects of glucocorticoids, such as poorly controlled diabetes mellitus, gastric and duodenal ulcers or electrolyte disorders, should be considered when using glucocorticoids [6]. However, such adverse effects are rare when used for a short duration following exclusion of patients with contraindications for glucocorticoids.

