Benefits to subjects will be directly related to the reduction of adverse effects of RAI provided that glucocorticoids are efficacious in reducing such effects. If the glucocorticoids are proven effective, this prophylactic measure could be incorporated to routine practice to minimize adverse effects of RAI. Potential risks would include potential adverse effects of short course of glucocorticoids; however, proton pump inhibitors will be concurrently administered to minimize gastrointestinal adverse effects. Other rare adverse effects include transient increased susceptibility to infections, transient hyperglycaemia, sleep disturbances, altered sensorium and mood changes. In the event of adverse effects to the subjects, medical or professional intervention will be sought. All participants will be educated about the adverse effects of RAI and the safety precautions that should be taken after administration.

If proven to be effective, short-term steroid prophylaxis could be made standard with the administration of RAI treatment for differentiated thyroid cancer which would minimize side effects and improve quality of life.

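### Logistic regression is fixed for every binary endpoint, including prednisolone harms expected to be rare, where it is unreliable if an arm has no events or very few (minor)

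*Protocol article*

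**What the plan says.** - **Method.** The Statistical analysis section states: "Comparisons between groups on binary endpoints will be performed using a logistic regression". It adds that analyses are adjusted for the stratification factors. The Randomization section defines three strata: "Criteria for stratification will be 50–100, > 100 and < 200, and > 200 mCi". The article does not say whether the p value comes from a Wald, likelihood-ratio or score test.
- **Reach.** The Secondary objectives include the effect of glucocorticoids on the incidence of glucocorticoid-related adverse effects. The Secondary endpoints list the same incidence. It is a yes/no outcome per patient, so the method sentence covers it.
- **Expected frequency.** The Discussion says: "Other rare adverse effects include transient increased susceptibility to infections, transient hyperglycaemia, sleep disturbances, altered sensorium and mood changes". No rates are given. Table 1 counts infection, altered sensorium and sleep disturbance from CTCAE grade 2, and hyperglycaemia and mood change from grade 3.
- **Other reporting.** Maximum grades per patient are tabulated for all adverse effects. The difference in proportions and odds ratio, with 95% CIs, are described for RAI-related effects; glucocorticoid effects are not named there.

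**The concern.** The method suits a primary endpoint expected in 10% to 20% of patients. The same sentence applies it to outcomes that may produce a handful of events or none in an arm of 200. With an empty arm, ordinary logistic regression has no finite odds ratio, and its usual tests err in opposite directions. The Wald test cannot reject however large the excess on the other arm, and the likelihood-ratio test rejects too readily.

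The Discussion proposes that prophylaxis could become standard if it is effective. That judgement needs a comparison of prednisolone harms that remains valid when events are few.

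**Working it through.** **1. The plan's own figure.** The inputs, from Sample size calculation, are 20% vs 10%, "At a 2-sided 5% alpha level", 80% power and 200 per group. With pooled variance and no continuity correction:

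n = [1.96·√(2·0.15·0.85) + 0.8416·√(0.20·0.80 + 0.10·0.90)]² / 0.10² = (0.990 + 0.421)² / 0.01 ≈ 199 per arm.

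The stated 200 reproduces (power 80.2%). At these rates about 40 and 20 events are expected, so logistic regression is sound for the primary endpoint.

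**2. Why an empty arm breaks the model.** With a events on prednisolone and b on placebo, the unadjusted odds ratio is a(200−b) / [b(200−a)]. At b = 0 the denominator is zero, the likelihood keeps rising as the log odds ratio grows, and software stops at an arbitrary large value. For 6 vs 0, adjusted for three strata (assumed 67/67/66 patients per arm, 2 events in each), the fit stops at log-OR 22.1 with SE about 15,000. So z ≈ 22.1/15,000 ≈ 0.0015 and p ≈ 0.999.

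**3. Results for 200 per arm with no placebo events.** Fisher is unstratified; the other columns adjust for the three strata.

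| Prednisolone vs placebo events | Wald p | Likelihood-ratio p | Fisher p | Firth OR (p) |
|---|---|---|---|---|
| 3 vs 0 | 0.999 | 0.041 | 0.248 | 7.0 (0.111) |
| 6 vs 0 | 0.999 | 0.004 | 0.030 | 13.3 (0.013) |
| 8 vs 0 | 0.999 | 0.0008 | 0.007 | 17.5 (0.003) |
| 10 vs 0 | 0.999 | 0.0002 | 0.0017 | 21.9 (0.0007) |

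A single placebo event restores a finite estimate: 8 vs 1 gives Wald p = 0.047.

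**4. How likely an empty placebo arm is.** P(no events) = (1 − p)^200, with p assumed:

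| Placebo rate | 0.25% | 0.5% | 1% | 2% | 3% |
|---|---|---|---|---|---|
| P(no events) | 61% | 37% | 13% | 1.8% | 0.2% |

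The chance of no placebo events together with at least 6 on prednisolone, at a true 3% on prednisolone, is 34%, 20% and 7% for placebo rates of 0.25%, 0.5% and 1%. At a true 2% on prednisolone it is 13%, 8% and 3%.

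**5. Chance of p < 0.05.** This enumerates two binomials of 200, unstratified, and counts Wald as non-rejecting when a cell is zero.

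| True rates, prednisolone vs placebo | Wald | Likelihood ratio | Fisher |
|---|---|---|---|
| 4% vs 0.5% | 27% | 78% | 56% |
| 4% vs 0.25% | 19% | 89% | 68% |
| 1% vs 1% (no difference) | 0.1% | 9.6% | 0.5% |

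The Wald test loses power as the placebo rate falls and the true excess grows. The likelihood-ratio test's power comes with a false-positive rate near twice the nominal 5% at 1% in both arms.

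**The case against.** **This belongs in the SAP.** Sparse-data fallbacks usually sit in the SAP, which is not shown, and their absence from an article is no finding. That is right as far as it goes. The point here is the stated sentence, which assigns one method to all binary endpoints. A fallback in the SAP would depart from it, so the sentence should leave room for one.

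**p near 1 is not inevitable.** A reader might infer that the plan would report any prednisolone-only harm with p near 1. The article does not support that. It names no test, and a likelihood-ratio test on the same model detects 6 vs 0. The non-finite odds ratio remains whichever test is used, and the likelihood-ratio test is itself too liberal here.

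**Empty arms may be uncommon.** The article calls these effects rare as consequences of a short steroid course, which is not a background rate on placebo. Infections needing intervention or moderate sleep disturbance may well occur among 200 placebo patients, and at 2% an empty arm is improbable. The article also does not commit to a separate model for each item, and a combined endpoint would rarely have an empty arm. This stands: the problem is confined to outcomes with placebo rates of about 1% or less.

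**The strata do not add to the failure.** It is tempting to say that three strata make it more likely. In a main-effects model they do not. Placebo events of 1/0/0 and prednisolone events of 0/3/2 across strata still give a finite log-OR of 1.63 (SE 1.10). Only an empty arm total makes the arm odds ratio infinite.

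**A second rarity statement does not apply.** The Discussion also says "such adverse effects are rare when used for a short duration", but that refers to poorly controlled diabetes, ulcers and electrolyte disorders, not the Table 1 list.

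**The harm would not be hidden.** Grades are tabulated, secondary analyses are to be fully reported, and the DSMB reviews safety every 8 weeks. A 6 vs 0 split would be seen; only its formal estimate and p value would mislead.

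**Conclusion.** The point holds in a limited form. The stated method covers harms that the article itself expects to be rare. With no events in an arm it yields no finite odds ratio and either an uninformative Wald p value or a likelihood-ratio p value that is too small. The chance of an empty placebo arm runs from 61% to 1.8% over assumed placebo rates of 0.25% to 2%.

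These figures rest on assumed event rates and on 200 patients per arm. The test comparisons also depend on which test is taken from the model, which the article leaves open. The documents do not support a claim that a harm would be concealed or that the primary comparison is at risk. Minor priority.

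**What to change.** In the Statistical analysis section, keep logistic regression for the primary endpoint and other common binary endpoints. Then add, in substance: for any binary endpoint with no events in an arm, or with few events in total (for example fewer than 10), counts per arm and the risk difference with a score-based 95% CI (Newcombe or Miettinen-Nurminen) will be reported, and the arms compared by a stratified exact test or Firth-penalised logistic regression. Choose one of the two tests in advance.

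Tie the rule to event counts, not to the glucocorticoid label. Table 1 attributes dyspepsia and abdominal pain to RAI or glucocorticoids, and Study assessments cites dyspeptic symptoms in around 50%, so dyspepsia would not need sparse-data methods.

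The cost is one or two sentences, using data already planned. The downsides are two methods across endpoints and the conservatism of exact tests (Fisher rejects about 0.5% of the time at 1% in both arms). The Trial status section says recruitment had not begun, so the wording could be settled before any data are seen.

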#### Secondary objectives

To estimate the impact of glucocorticoids on the incidence of early and intermediate adverse effects of RAI during the first 3 months post therapy (all types, all grades, any duration).To describe comparatively between treatment and control groups the onset, duration, recurrence and severity of early and intermediate adverse effects of RAI during the first 3 months after completion of RAITo evaluate the impact of glucocorticoids on the incidence, severity and type of all adverse effects assessed as related to glucocorticoidsTo evaluate the impact of glucocorticoids on the patient-reported outcomes related to adverse effects of RAI at 2 weeks and 3 months after completion of RAITo study the impact on the quality of life at 2 weeks and 3 months, first overall between treatment groups, then focusing on patients who have experienced a complication of RAI

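### The unqualified t-test rule for continuous endpoints also covers duration (and timing of onset) of adverse effects, values that exist only in patients with an event; it should be limited to the quality-of-life scores

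*Protocol article*

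**What the plan says.** Four places in the protocol article bear on this point.

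- **Statistical analysis.** Binary endpoints are compared by logistic regression. For the rest, "comparisons between groups on continuous endpoints will be performed using" t tests. No continuous endpoint is named and none is excepted. Secondary analyses get no multiplicity adjustment and are to be reported in full.
- **Secondary endpoints.** One item groups onset, duration, recurrence and CTCAE severity of the Table 1 effects. EQ-5D-5L and FACT H&N scores are a separate item.
- **Secondary objectives.** The matching objective is "To describe comparatively between treatment and control groups the onset, duration, recurrence and severity of early and intermediate adverse effects of RAI". The other secondary objectives speak of estimating, evaluating or studying an impact.
- **Sample size calculation.** For the control rate, "we assume that clinically significant adverse effects will be reported at 3 months in 20% of patients"; the assumed rate on prednisolone is 10%.

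The article gives no value for duration or onset time to a patient who has no adverse effect.

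**The concern.** Duration is continuous, and so is onset if it means time to onset. Neither exists for an event-free patient. A t test on them therefore uses only patients who had an event, and having an event is the very outcome prednisolone is meant to change. The groups being compared are no longer those that were randomised.

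The direction of the result is at stake. If the drug prevents short events more than long ones, the events left in its arm are longer on average. A trial with a favourable primary result could then also report a p value for longer duration on prednisolone, even though its patients had fewer days with symptoms.

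**Working it through.** **1. The plan's own figure.** Inputs from Sample size calculation: 20% against 10%, two-sided 5% alpha, 80% power. With the pooled-variance formula,

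n = [1.96 × √(2 × 0.15 × 0.85) + 0.842 × √(0.20 × 0.80 + 0.10 × 0.90)]² / 0.10² ≈ 199 per arm.

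The stated 200 is reproduced (power 80.2%), so the planning rates can be used below.

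**2. How many patients have a value.** Events = 200 × rate in each arm; unscored share = 1 − (sum of events)/400.

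| Event set | Control vs prednisolone | Patients with a value | Unscored |
|---|---|---|---|
| Clinically significant (planning rates) | 20% vs 10% | 40 vs 20 | 340/400 = 85% |
| Any grade (assumed) | 50% vs 40% | 100 vs 80 | 220/400 = 55% |
| Any grade (assumed) | 67% vs 57% | 134 vs 114 | 152/400 = 38% |

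The assumed control rates echo figures the article quotes for single symptoms: around 50% for dyspeptic symptoms, and 67% as the upper end for acute sialadenitis. The prednisolone rates are assumed 10 points lower.

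**3. Precision.** Difference detectable with 80% power, in SD units: (1.96 + 0.842) × √(1/n₁ + 1/n₂). This is 0.28 with 200 per arm and 0.77 with 40 against 20.

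**4. Direction.** All durations and the split of events here are assumptions. The drug leaves the length of any given event unchanged.

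Scenario A: short events average 5 days and long events 25. Control has 10% short and 10% long; prednisolone has 2% short and 8% long.

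- Mean among patients with an event: control (0.10 × 5 + 0.10 × 25)/0.20 = 15.0 days; prednisolone (0.02 × 5 + 0.08 × 25)/0.10 = 21.0 days. Apparent harm: +6.0 days.
- Mean per randomised patient, 0 if event-free: 3.0 against 2.1 days. Benefit: −0.9 days.
- In simulated trials with gamma durations (shape 4), the events-only t test is significant in the wrong direction in about 36%. A rank test on symptom-days in all 400 patients detects the benefit in roughly three quarters.

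Scenarios B to E use short events averaging 7 days and long events 28 (coefficient of variation 0.5). In B to D control has 10% short and 10% long; in E it has 30% short and 20% long.

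| Scenario | Cut in short / long events | Events-only difference | Significantly longer on prednisolone | Symptom-days per randomised patient |
|---|---|---|---|---|
| B | 90% / 10% | +8.4 days | 53% | −0.9 |
| C | 75% / 25% | +5.3 days | 25% | −1.2 |
| D | 50% / 50% | about 0 | 2.8% | −1.7 |
| E, any grade | 50% / 0% | +3.6 days | 38% | −1.05 |

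Scenario D is the control case. With equal prevention the wrong-direction rate is close to the nominal 2.5%, so the bias comes from unequal prevention alone.

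**The case against.** The strongest reply is that the protocol never says t tests will be run on onset or duration. The sentence names no endpoint and fits EQ-5D-5L and FACT H&N, which every patient can have. The matching objective is the one secondary objective worded as description. This stands in part. A reader might infer that a t test on duration is an express plan; it is not. It is what an unqualified rule yields when applied to a listed endpoint, and that is why the two sections should be reconciled.

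Onset may also mean occurrence, as it does in the primary outcome, and occurrence is defined for everyone. Study assessments lists onset beside duration and rate, which suggests timing but does not settle it. The point is therefore firm for duration and conditional for onset.

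A reader might take 80 to 90% unscored as the general figure. It holds only for clinically significant effects at the planning rates.

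The reversal needs unequal prevention, which nothing in the article establishes. Also, under the endpoint definitions most symptoms below the Table 1 grade count as clinically significant only if they last more than 2 weeks, so many mild short events fall outside the 20%. That weakens a mild-against-severe story. A short event that reaches the Table 1 grade still counts, however, and the any-grade scenario shows the same selection.

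A reader might see a breach of intention to treat. The documents do not support that: the all-randomised rule is stated for the main analyses, and incidence is defined for every patient.

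Finally, an analysis plan not shown here may settle the detail. The point rests on a rule the article does state, not on missing detail.

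**Conclusion.** The point holds in this limited form. Applied as written, the t-test rule would put a p value on duration, and on onset if read as timing, in subsets selected after randomisation. About 85% of patients would be unscored for clinically significant effects, and about 40 to 55% at the assumed any-grade rates.

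The direction can reverse if short events are prevented preferentially: +3.6 to +8.4 days against prednisolone, and wrong-direction significance in 25 to 53% of trials, across the unequal scenarios. These figures rest on assumed durations and splits and show what can happen; they are not a forecast. With equal prevention there is no such bias.

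One secondary endpoint is concerned. The primary endpoint, a proportion in all randomised patients, and the sample size are untouched. The change should be made, but the trial's main conclusion does not depend on it.

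**What to change.** In Statistical analysis:

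1. Limit t tests to the EQ-5D-5L and FACT H&N scores.
2. State that onset timing and duration among affected patients are described by arm without a p value, in line with the objective.
3. For any between-arm comparison, use measures defined for every randomised patient. For duration: symptom-days over the 3 months, 0 if event-free, with a rank-based or permutation test stratified by RAI dose. For onset: cumulative incidence of first onset over 3 months.

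The cost is one or two sentences. The diary and clinical interviews already planned supply the data, and recruitment had not begun at publication. The small downside is that symptom-days mix frequency and duration, and with many zeros a rank test responds largely to frequency. Both parts should therefore be tabulated beside it.
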